## Abstract

**Background:**

The patellofemoral joint (PFJ) is one compartment of the knee that is frequently affected by osteoarthritis (OA) and is a potent source of OA symptoms. However, there is a dearth of evidence for compartment-specific treatments for PFJ OA. Therefore, this project aims to evaluate whether a physiotherapy treatment, targeted to the PFJ, results in greater improvements in pain and physical function than a physiotherapy education intervention in people with symptomatic and radiographic PFJ OA.

**Methods:**

90 people with PFJ OA (PFJ-specific history, signs and symptoms and radiographic evidence of PFJ OA) will be recruited from the community and randomly allocated into one of two treatments. A randomised controlled trial adhering to CONSORT guidelines will evaluate the efficacy of physiotherapy (8 individual sessions over 12 weeks, as well as a home exercise program 4 times/week) compared to a physiotherapist-delivered OA education control treatment (8 individual sessions over 12 weeks). Physiotherapy treatment will consist of (i) quadriceps muscle retraining; (ii) quadriceps and hip muscle strengthening; (iii) patellar taping; (iv) manual PFJ and soft tissue mobilisation; and (v) OA education. Resistance and dosage of exercises will be tailored to the participant's functional level and clinical state. Primary outcomes will be evaluated by a blinded examiner at baseline, 12 weeks and 9 months using validated and reliable pain, physical function and perceived global effect scales. All analyses will be conducted on an intention-to-treat basis using linear mixed regression models, including respective baseline scores as a covariate, subjects as a random effect, treatment condition as a fixed factor and the covariate by treatment interaction.

**Conclusion:**

This RCT is targeting PFJ OA, an important sub-group of knee OA patients, with a specifically designed conservative intervention. The project's outcome will influence PFJ OA rehabilitation, with the potential to reduce the personal and societal burden of this increasing public health problem.

**Trial Registration:**

Australia New Zealand Clinical Trials Registry ACTRN12608000288325

## Background

Osteoarthritis (OA) is the leading cause of musculoskeletal pain and disability and is the third leading cause of life-years lost due to disability in Australia, only behind depression and dementia [1]. The annual total cost of arthritic disease in Australia is estimated at $24 billion [2], with the knee joint contributing substantially to this overall cost. The prevalence of OA in people aged over 55 years is 20–26% and rising, with arthritis rates expected to increase by 30% over the next 40 years [2]. The pain and suffering endured by patients as a result of OA decreases their quality of life, with the annual burden of disease costs ($12 billion in Australia) being half the total costs associated with this condition [2]. Pain associated with daily activities such as walking and stair-climbing ultimately leads to profoundly reduced functional independence [2].

The patellofemoral joint (PFJ) is one of the three knee joint compartments. Awareness of its importance in the OA process has been raised by the increasing use of lateral and skyline x-rays in recent times. Research has revealed that PFJ OA is more common than previously thought. In a community-based study of knee OA (N = 218), the frequency of radiographic osteophytes was greater in the PFJ (65% knees) than in the tibiofemoral joint (TFJ) (55% knees) [3]. Furthermore, in people with knee pain (N = 777), the most common compartmental distribution of radiographic OA was a combination of TFJ and PFJ disease (40%), followed by isolated PFJ OA (24%), and isolated TFJ disease (4%) [4]. Within the PFJ, the lateral compartment is more frequently affected by the OA process than the medial [5,6]. Importantly, the presence of baseline PFJ OA predicts structural deterioration in the TFJ compartment over 30 months (OR 2.31, 95% CI 1.37, 3.88) [7].

The PFJ is an important source of symptoms associated with knee OA [8]. Knee pain has been found to be significantly associated with PFJ osteophytes (OR 2.25, 95%CI 1.06, 4.77), but not TFJ osteophytes (OR 1.19, 95% CI 0.46, 3.09) [9], suggesting that the PFJ may be a more important source of knee pain than the TFJ. Hunter et al [10] noted that increased pain and poorer function was associated with reduced cartilage volume in the patella, but not in the femur nor the tibia. Other authors have confirmed the relationship between radiographic PFJ OA and knee pain [11-13].

Management strategies for knee OA have traditionally focussed on alleviating symptoms, primarily using drug therapies or surgery. A meta-analysis of OA trials highlights this, with most trials evaluating drug treatments (60%) or surgical procedures (26%) [14]. OA experts have highlighted the overall dearth of quality evidence to support the use of non-pharmacological interventions such as physiotherapy. Despite this, knee OA clinical guidelines recommend that conservative treatments be included as a first line strategy for the optimal management of the disease [15,16]. Physiotherapy is a conservative intervention, which is non-toxic, inexpensive and promotes physical activity and self management through exercise. Therefore, rigorous randomised clinical trials (RCTs) that evaluate the efficacy of physiotherapy are clearly needed, to better guide clinical decision-making.

Given the heterogeneity of knee OA with regard to aetiology, clinical presentation and natural history, guidelines also recommend the tailoring of knee OA treatments to the location of joint damage in order to optimise treatment outcomes [15,16]. However, most trials of physiotherapy for knee OA have not been targeted to disease subgroups, with participant selection typically based on the presence of non-specific knee pain and radiographic changes anywhere on an anteroposterior radiograph. While a plethora of evidence attests to the benefits of exercise for patients with predominant TFJ OA [17] there is no level I evidence and only one RCT [18] specifically addressing the problem of PFJ OA. The dearth of evidence for a compartment-specific treatment for PFJ OA necessitates our proposed study to establish the efficacy of a compartment-specific physiotherapy treatment using the rigour of a RCT.

While there is little known about the physical impairments associated with PFJ OA, there are several RCTs that have evaluated physical interventions for PFJ pain in younger adults (patellofemoral pain syndrome, or anterior knee pain). We have previously conducted a double blind, placebo-controlled RCT [19], which demonstrated the efficacy of a targeted physiotherapy program for this patient population. The targeted treatment involved (i) quadriceps muscle retraining; (ii) patellar taping; (iii) manual PFJ and soft tissue mobilisation; and (iv) hip muscle retraining. We have recently confirmed the beneficial effects of this targeted physiotherapy approach on pain and physical function in another population of young adults with PFJ pain [20]. Therefore, we are proposing to evaluate a similar, targeted physiotherapy intervention for people with PFJ OA.

This project aims to evaluate whether a physiotherapy treatment, targeted to the PFJ and based on successful treatment for PFJ pain in younger populations, results in greater improvements in pain and physical function than a physiotherapy education intervention in participants with symptomatic and radiographic PFJ OA.

## Methods

### Experimental design

A randomised, single-blind, controlled clinical trial conforming to CONSORT [21] guidelines will be conducted, comparing a multimodal physiotherapy intervention to a physiotherapy education intervention (Figure 1). A Project Investigator will screen for eligibility based on history, clinical and radiographic examination.

**Figure 1 F1:**
[figure not shown]
Flow of participants through the randomised controlled trial.

Ethical approval has been obtained from the University of Melbourne Human Research Ethics Committee (HREC No. 0721163) and from the Department of Human Services Victoria, Radiation Safety Committee. All participants will provide written informed consent.

### Participants

Ninety people with lateral PFJ OA will be recruited from the community via advertisements, medical practitioners and our own research database. To be included in the study, participants must fulfil the following criteria: (i) aged > 40 years; (ii) anterior- or retro-patellar knee pain aggravated by at least two activities that load the PFJ (eg stair ambulation, squatting and/or rising from sitting); (iii) pain severity ≥ 4 on an 11 point numerical pain scale during aggravating activities; (iv) pain during these activities present on most days during the past month; (v) osteophyte grade ≥ 1 in the lateral PFJ compartment on skyline x-ray [22].

Exclusion criteria will include: (i) concomitant pain from other knee structures, hip or lumbar spine; (ii) current or previous physiotherapy for knee pain (prior 12 months); (iii) contra-indications to the treatments (eg tape allergy); (iv) recent knee injections (prior 3 months); (v) planned lower limb surgery in the following 9 months; (vi) body mass index ≥ 35 kg.m^2^; (vii) medial PFJ OA (osteophytes or joint space narrowing on a skyline x-ray) that is more severe than lateral PFJ OA; (viii) moderate to severe concomitant TFJ OA (Kellgren and Lawrence grade ≥ 3 on an anteroposterior radiograph) [23]; (ix) knee or hip arthroplasty or osteotomy; (xi) physical inability to undertake testing procedures or; (x) inability to understand written and spoken English.

### Sample Size

Treatment efficacy will be evaluated by comparing change on primary outcome measures between groups. We aim to detect the minimum clinically important improvement on these outcomes as reported by Tubach et al [24]. Specifically, a sample of 90 will provide a minimum of 90% power (α = 0.05) to detect a difference in pain on visual analogue scale (VAS) of 19.9 (21.5) mm and a difference in physical function on the Western Ontario MacMaster Universities Osteoarthritis Index (WOMAC) [25] of 9.1 (13.9) normalised units. This sample size also allows for an estimated 10% drop-out rate.

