### Data quality and management

Strategies employed to ensure data quality include: (i) training of assessors and physiotherapists; (ii) assessment of procedural quality; (iii) random checks by investigators of adherence to study protocols; and (iv) random checks of forms for completeness and data for accuracy. All analyses will be conducted on an intention-to-treat basis. The primary outcomes measured at 12 weeks and 9 months will be analysed using linear mixed regression models, including their respective baseline scores as a covariate, subjects as a random effect, treatment condition as a fixed factor and the covariate by treatment interaction. Participant characteristics (eg; gender, radiographic severity of TFJ and PFJ OA) will also be included as covariates. Regression diagnostics will be used to check for normality of the measures and homogeneity of variance, where appropriate. Comparisons between group means will be performed using Bonferroni or Newman Keuls range tests. An alpha level of 0.05 will be used. Calculation of the number needed to treat index will be performed to facilitate the development of clinical guidelines.

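### The stated minimum of 90% power is not reached for WOMAC function under a conventional two-sided 5% comparison (about 83% after drop-out); it needs a one-sided alpha or an unstated gain from adjustment

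*Protocol article*

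**What the plan says.** The Sample Size section bases the trial on the between-group comparison of change in the primary outcomes. It states that "a sample of 90 will provide a minimum of 90% power (α = 0.05"). Two target effects are named. The pain target is "a difference in pain on visual analogue scale (VAS) of 19.9 (21.5) mm"; the target for WOMAC physical function is "9.1 (13.9) normalised units". On attrition, the section says: "This sample size also allows for an estimated 10% drop-out rate". The word minimum makes 90% a floor for both outcomes, and the last sentence means that the floor should survive the drop-out.

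The section does not say whether alpha is one-sided or two-sided, which test was used for sizing, or whether a gain from baseline adjustment was counted.

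The analysis paragraph, under Data quality and management, says "An alpha level of 0.05 will be used", again without sidedness. It plans linear mixed models for the 12-week and 9-month outcomes with the baseline score as a covariate, and adds: "Comparisons between group means will be performed using Bonferroni or Newman Keuls range tests". The aim in the Background is worded in one direction: whether the treatment "results in greater improvements in pain and physical function than a physiotherapy education intervention".

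**The concern.** The two outcomes have quite different standardised effects: 0.93 for pain and 0.65 for WOMAC function. A sample that gives just 90% power for the smaller effect would give far more for the larger, so the claim stands or falls on WOMAC function. With about 40 completers per arm, a standardised effect of 0.65 looks too small for 90% power in a two-sided 5% test.

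WOMAC function is a primary outcome. If the unadjusted two-sided reading is the intended one, the chance of missing a true 9.1-unit difference after drop-out is about 17%, not the 10% at most that the section implies. Readers of a non-significant function result would then be working from a power figure that the trial did not have.

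**Working it through.** **Inputs.** From the Sample Size section: N = 90, alpha 0.05, WOMAC difference 9.1 with 13.9 in brackets, VAS difference 19.9 with 21.5 in brackets, drop-out 10%. Assumed here: the bracketed figures are the SDs that apply to the between-group comparison, and allocation is 1:1 (45 per arm). Completers: 90 × 0.9 = 81, split 41/40.

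**Formula.** Standardised difference d = difference / SD. Noncentrality = d / √(1/n₁ + 1/n₂). Power comes from the noncentral t distribution with n₁ + n₂ − 2 degrees of freedom.

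- WOMAC: d = 9.1 / 13.9 = 0.655
- VAS: d = 19.9 / 21.5 = 0.926

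**Reproducing the plan's figure.** With a one-sided 0.05 test and the normal approximation, n per arm for WOMAC is 2 × (1.645 + 1.282)² / 0.655² = 40 after rounding up. That is 80 evaluable, and 80 / 0.9 = 89 randomised, almost exactly the 90 stated. The figure is therefore reproduced, but only under a one-sided alpha.

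**Two-sided 0.05.** For WOMAC with 45/45, the noncentrality is 0.655 / √(2/45) = 3.11 and the critical value is 1.987. With 41/40, they are 2.95 and 1.990.

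| Outcome | Test | 90 participants (45/45) | 81 completers (41/40) |
|---|---|---|---|
| VAS pain | two-sided | 99.1% | 98.4% |
| WOMAC function | two-sided | 86.7% | 82.9% |
| WOMAC function | one-sided | 92.5% | 89.9% |

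The normal approximation gives slightly higher WOMAC values: 87.4% and 83.8% two-sided, and 92.8% and 90.3% one-sided. The choice of approximation does not explain the two-sided gap.

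For scale, two-sided 90% power for WOMAC without adjustment needs 100 evaluable (normal) or 102 (t). Divided by 0.9, that is 112 or 114 randomised.

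**Can the planned baseline adjustment close the gap?** With 81 completers and a single follow-up, two-sided 90% power needs a residual SD of about 12.5 or less, a factor of 12.48 / 13.9 = 0.898. Let r be the correlation between baseline and follow-up, with equal variances at both times.

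- If 13.9 is a cross-sectional SD, the residual SD is 13.9 × √(1 − r²). The condition is r ≥ √(1 − 0.898²), which is about 0.44.
- If 13.9 is an SD of change, the residual SD is 13.9 × √((1 + r)/2), which rises with r. The condition is r ≤ 2 × 0.898² − 1, which is about 0.61. On this reading, power with 41/40 is 95.0% at r = 0.3, 91.9% at 0.5, 90.2% at 0.6 and 88.4% at 0.7.

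The article gives no value of r and does not say which kind of SD 13.9 is.

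**The case against.** The strongest reply is that the planned analysis is not an unadjusted t test. The model adjusts for baseline and uses both follow-up visits, and the sizing is framed in terms of change. If 13.9 is an SD of change, adjustment alone keeps power at 90% or more for any correlation from 0 to about 0.61, which is an ordinary range. Pooling two visits could add to this. As an illustration with assumed values, take 13.9 as a cross-sectional SD, a correlation of 0.6 between follow-ups, 0.3 with baseline at each visit, and the same 9.1-unit effect at both. The residual SD is then 13.9 × √(0.8 − 0.09) = 11.7, and power with 81 completers is about 93%. This part of the reply stands: the planned model may well deliver 90%. What it does not do is support the printed figure, because the Sample Size section claims no such gain and gives nothing from which to compute one.

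The second reply is that sidedness is not stated, the aim is directional, and a one-sided test reproduces the sample size. This stands in part. Two-sided is the conventional reading of an unqualified 0.05, but it is not one of the article's own inputs, so the figure cannot be called an outright arithmetic error. On the other hand, a directional aim is not a test specification, and the Newman-Keuls range tests named in the analysis paragraph are non-directional. One-sided sizing would not match them.

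A reader might also infer that Bonferroni correction across the three primary outcomes lowers the power further. The article does not support this. It attaches Bonferroni to comparisons between group means, does not apply it across outcomes, and keeps alpha at 0.05.

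**Conclusion.** The concern holds in a limited form. Under a two-sided 0.05 comparison of change with 1:1 allocation and the bracketed figures as SDs, the stated minimum of 90% is met for pain with room to spare. It is missed for WOMAC function, by about 3 percentage points with all 90 participants (86.7%) and about 7 after the planned drop-out (82.9%). The stated figure is recovered only by a one-sided alpha of 0.05, and then just at the boundary (89.9% by t, 90.3% by normal approximation), or by an efficiency gain that the section does not state.

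A reader might go further and conclude that the trial is underpowered for function or must recruit about 114 people. The article does not support that, because the baseline-adjusted repeated-measures model could plausibly reach 90% with the present number. The defect is a power statement that does not follow from the assumptions given with it.

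**What to change.** Keep N = 90 and reword the Sample Size paragraph:

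- State that alpha is two-sided.
- Give power per outcome after drop-out. Suggested text: with 90 randomised and 81 completers, an unadjusted two-sided 0.05 comparison has about 98% power for a VAS pain difference of 19.9 mm (SD 21.5) and about 83% for a WOMAC function difference of 9.1 units (SD 13.9).
- If the 90% relies on baseline adjustment or on the two follow-up visits, state whether 13.9 is a cross-sectional SD or an SD of change, the assumed correlations, and the resulting power.
- If it relies on a one-sided test, say so and reconcile that with the range tests in the analysis paragraph.

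The cost is one paragraph. No extra participants are needed. Unless an adjustment gain is documented, the stated WOMAC power becomes less favourable.

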### Procedure

The randomisation schedule (permuted blocks of 8 to 12) will be generated and maintained centrally by one of the investigators (BV), who will not be involved in assessment of participants. The randomisation schedule will be revealed via telephone following baseline assessment. A blinded investigator will perform outcome assessments (Table 1) at baseline, 12 weeks and 9 months, and participants will be instructed not to divulge their group allocation. Security of the blinding system will be evaluated to ensure integrity.

**Table 1 T1:** Outcome measures used in the randomised controlled trial

**Primary Outcome**	**Measurement**
Usual pain on movement in the previous week	0–100 mm visual analogue scale (VAS) with terminal descriptors: 0 = no pain; 10 = maximal pain
Usual pain during nominated aggravating activity in the previous week	0–100 mm visual analogue scale (VAS) with terminal descriptors: 0 = no pain; 10 = maximal pain
Self reported difficulty with physical function	Physical Function subscale of the Western and Onatario MacMasters University (WOMAC) Osteoarthritis Index (Likert version)

**Secondary Outcomes**	**Measurement**

*Symptoms*	
Pain and stiffness	Pain and Stiffness subscales of the WOMAC
Perceived global effect score	5 point ordinal scale (1-much improved; 2-improved. 3-same; 4-worse; 5-much worse)
Sports and recreation function	Sports and recreation function dimension of the Knee Injury and Osteoarthritis Score (KOOS)
Symptoms	Symptoms dimension of the KOOS
Knee related quality-of-life	Knee related quality-of-life dimension of the KOOS
*Function*	
Lower extremity functional performance	One-leg rise test – maximum number of one-leg rises from sitting on a 0.48 m stool
Stair ambulation performance	Timed stair ascent and descent
Standing balance	Step test – number of times can step foot up and down off 15 cm step in 15 s

**Other Outcomes**	**Measurement**

Physical activity levels	Physical Activity Scale for the Elderly (PASE)
Adherence (physiotherapy group only)	Number of physiotherapy visits Completion of home exercises via log-book
Knee-related medication use	Log-book
Adverse effects	Log-book and open probe questioning

### Outcome assessment

Age, gender, duration of knee OA symptoms, previous treatment, surgery and medication use for knee OA will be obtained at the baseline assessment.

#### Primary outcome measures: Pain and physical function

Overall average *knee pain *in the previous week on movement and during an aggravating activity nominated by the participant will be self-assessed with a 0–100 mm horizontal visual analogue scale (VAS) with terminal descriptors of (0 = no pain; 10 = maximal pain). Self-reported difficulty with *physical function *will be assessed using the physical function subscale of the Likert version of the WOMAC [25]. This disease-specific measure is reliable, valid and responsive and comprises 17 items, using a 5-point scale to score each, where higher scores indicate worse symptoms.

#### Secondary outcome measures

*Pain and stiffness *will be assessed using the relevant subscales of the WOMAC [25]. Participants will rate their perceived overall change in symptoms following treatment on a 5 point ordinal scale: 1-much improved, 2-improved, 3-no change, 4-worse, 5-much worse, giving a *perceived global effect score*. *Sports and recreation function, symptoms *and *knee-related quality-of-life *will be assessed using the relevant dimensions of the Knee Injury and Osteoarthritis Outcome Score (KOOS) [26].

*Objective measures of function *will include the one-leg rise test, a timed stair ambulation test and the step-test. The one-leg rise test is the maximum number of one-leg rises the participant can perform from sitting on a stool. The participant must hold their non-test leg out straight and cannot use their arms for assistance. The number of rises that the participant can complete will be recorded. This test is a measure of lower extremity functional performance that has been found to predict the development of radiographic knee OA in middle aged people with chronic knee pain [27]. The timed stair ambulation task involves the participant ascending and descending a set of nine standard steps at their usual pace and the total time taken recorded, with longer time taken indicating poorer physical function [28]. The step-test is a functional, dynamic test of standing balance, where the participants stands on one leg in front of a 15 cm step, and places the opposite foot on and off the step as quickly as possible over 15 seconds. The total number of successful steps are recorded, with higher scores indicating better balance [29].

